### Consent and Confidentiality:

Participation in the study will be voluntary; trained interviewers will administer informed consent to the participants. Strict confidentiality and privacy will be ensured. Participants will be anonymized in data to protect their identity and password-protected primary servers, mobile devices, and end-to-end encryption WhatsApp; all these measures will be used. Information regarding data security and protection will be provided to participants. There is also a contingency plan to change the intervention strategy for SMS and voice calls in the case of internet connection problems and WhatsApp connectivity or failures.

### Reporting of Adverse Events:

We will document any additional adverse effects relating to participants other than the primary and secondary outcomes.

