**Methods::**

Twleve months duration long randomized controlled trial from January to December 2021 will be carried out at Shaikh Zayed Medical Complex (SZMC), Lahore. A total of 440 patients aged 18 years and older diagnosed with hypertension in the last month with non- adherence to antihypertensive therapy <80% of pills used in the last 30 days and have access to a smartphone will be randomized into either the intervention group (n=220) or the control group (n=220). For the intervention arm, a comprehensive intervention, the “Multi-Aid-Package,” consisting of seven items: written, voice, and graphics messages, animated video, educational material, and a 24/7 help service, has been designed. Standard care will be provided to the control group. The primary outcome will be improved adherence to antihypertensive medication, while the secondary outcome will be an alteration in systolic blood pressure (SBP). The analysis will be intention to treat.

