## METHODS

This study is 12 months duration long overall from January to December 2021, including six months follow up period, two-arm, single-blinded, intention-to-treat randomized controlled trial. The evaluation will be performed at the pretest and posttest. This trial is designed in accordance with the SPIRIT 2013 guidelines (Fig.1).^15^

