### Control Arm:

Participants in the control group receive conventional care only. No intervention/ placebo will be provided to controls. There will be no way to keep them engaged except follow-ups.

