### Outcome Measures

### Primary Outcome:

The change in adherence to antihypertensive medication will be the primary outcome. The primary endpoint will be assessed using the SEAMS and pill counts used over a certain period.^14^,^16^ The adherence to antihypertensive medication will be assessed at baseline and six months.

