### Secondary Outcome:

The change in SBP will be the secondary outcome. Two readings will be taken, and the final measurement is the average of the two. Systolic blood pressure will be assessed at baseline and six months.

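### The adverse-event rule can be read to leave out blood-pressure events and tablet over-use, and unequal contact between arms may make spontaneous reports uneven

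*Protocol article*

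**What the plan says.** All references are to the protocol article.

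- **Reporting of Adverse Events**, the only text on the subject: "We will document any additional adverse effects relating to participants other than the primary and secondary outcomes". It speaks of participants in general and names no arm.
- **Primary Outcome**: "The change in adherence to antihypertensive medication will be the primary outcome". It is measured by the SEAMS score and pill counts at baseline and six months.
- **Secondary Outcome**: "The change in SBP will be the secondary outcome", with "Systolic blood pressure will be assessed at baseline and six months". METHODS agrees on timing: "The evaluation will be performed at the pretest and posttest".
- **Data Collection**: the pill measure is the ratio of tablets taken to tablets prescribed. A value of 80% or more is adherent, and no upper bound is given. The four questionnaire sections cover health and sociodemographics, SEAMS, pills used, and acceptability of the intervention.
- **Contact, intervention arm**: the abstract lists "educational material, and a 24/7 help service, has been designed" among the package contents, and Table-I, item 7, lists optional help from a doctor.
- **Contact, control arm**: conventional care, and "There will be no way to keep them engaged except follow-ups".
- **Blinding**: data collectors and outcome evaluators do not know the allocation.

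**The concern.** The intervention is meant to make patients who miss their antihypertensives take them. If it works, its most plausible harms lie in the two domains that the outcomes occupy: blood pressure and tablet intake. A rule that documents adverse effects apart from those outcomes invites staff to treat an event in either domain as already covered, and so not to record it.

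A second weakness adds to this. One arm can reach a doctor at any hour and the other cannot, so events that patients volunteer may reach the study more readily from the intervention arm.

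At stake is whether the report can set a sound account of harms beside any gain in SBP. The Discussion says that a fall in SBP would be a significant improvement in settings with limited resources, and the Conclusion recommends that the package be considered in comparable countries.

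**Working it through.** The plan states no figure on this point, so the check is mainly one of wording.

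**Step 1. What the rule sets apart.** The rule covers additional effects apart from the primary and secondary outcomes. Two readings are open:
- *Narrow*: anything belonging to the domain of an outcome (blood pressure, tablet intake) is not documented as an adverse effect.
- *Wide*: the study documents adverse effects on top of the outcome data, whatever their domain.

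Nothing else in the article decides between them.

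**Step 2. Whether the outcome data would show these events as harms under the narrow reading.**

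| Event | Where outcome data could show it | What happens there |
|---|---|---|
| Blood-pressure event between visits | SBP at baseline and six months | No SBP assessment is stated in between. SBP is then compared as a continuous variable (t-test or Mann–Whitney), so an episode that has resolved leaves no trace. |
| Tablet over-use | Pills taken ÷ pills prescribed | Over-use in the counted period gives a ratio above 100%. That exceeds 80%, so the patient is classed as adherent: a success, not a harm. |

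**Step 3. Contact by arm.** Intervention: help service and optional doctor help, besides follow-up. Control: follow-up only. As the article describes the questionnaire, no section asks about adverse events, and end-user suggestions are sought from the intervention arm only. The described contact therefore differs, and no prompt common to both arms is described.

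**Step 4. What uneven capture could do (assumed values, for scale only).** The documents give neither event rates nor capture rates. Assume the same true event proportion p in both arms, 90% of events captured in the intervention arm, and 70% or 50% in the control arm. Then:

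observed proportion = p × capture; spurious ratio = 0.90/0.70 = 1.29, or 0.90/0.50 = 1.8.

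The last column is the chance that a two-sided 5% test of two proportions, with 220 per arm (Sample Size section), shows a significant excess in the intervention arm. With equal capture it would be nominally 2.5%.

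| True p, both arms | Control capture | Observed, intervention v control | Chance of a false excess |
|---|---|---|---|
| 5% | 70% | 4.5% v 3.5% | about 8% |
| 10% | 70% | 9% v 7% | about 12% |
| 20% | 70% | 18% v 14% | about 21% |
| 5% | 50% | 4.5% v 2.5% | about 21% |
| 10% | 50% | 9% v 5% | about 38% |
| 20% | 50% | 18% v 10% | about 68% |

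The 220 is the number planned per arm including the 30% attrition allowance; with fewer patients analysed these chances would be smaller. If capture were equal, the ratio would be 1.

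**The case against.** The strongest reply is that the outcomes set apart are *changes* in two measured quantities. A faint, a fall or a hypertensive emergency is not a change in SBP, and the word additional naturally means beyond the outcome data. On that reading such events fall inside the rule. This stands as a fair reading, and it rules out the inference that blood-pressure harms will go unrecorded: they may, if staff take the narrow reading. Six-month SBP is also recorded without restriction to one arm.

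On over-use, the reply is that a ratio above 100% would be visible in the pill data. That is so for the counted period, but the stated classification turns it into adherence, so it would not be seen as a harm.

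A reader might also infer that only the intervention arm can report events. The article does not support that: the help service is package content and is nowhere named as an adverse-event route, the rule is not specific to one arm, and controls have follow-ups at which they could report. Nor can the safety comparison be called lopsided, because the article defines no between-arm comparison of adverse events.

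Finally, an article commonly leaves the method, timing and grading of adverse-event collection to the full protocol, so their absence is no fault here. That stands too. The point rests on the sentence the article does state and on the contact it does describe.

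**Conclusion.** The point holds as a matter of ambiguity and risk. The stated rule can be followed in a way that drops blood-pressure events and tablet over-use, and under that reading the outcome data would not show them as harms. Described contact differs by arm, so spontaneously reported events may be captured unevenly.

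The size is unknown. The illustrated ratios of 1.29 to 1.8 rest wholly on assumed capture rates and equal true event rates; they show that moderate differences in capture could matter, not that they will occur. The schedule and flow-chart figures were not available to this review, so any interim contact shown there has not been considered. The change is a cheap improvement worth making, not the repair of a demonstrated bias.

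**What to change.** 1. In Reporting of Adverse Events, delete the clause that excepts the primary and secondary outcomes. State that blood-pressure-related events and tablet over-use are recorded as adverse events whatever their outcome status.
2. Have the blinded data collectors ask both arms the same adverse-event questions at the existing six-month visit. These are best put before the acceptability section, since end-user suggestions come from the intervention arm only and could reveal the allocation.
3. Base any between-arm comparison of adverse events on those answers alone.
4. List separately the events learned only through the help service, and keep that list from the blinded collectors.

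The cost is one edited sentence, a few added questions and a slightly longer interview. The main downside is reliance on recall over six months. Because participants know what they received, recall may still differ between arms; asking the same questions reduces uneven capture but does not remove it.

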## DISCUSSION

The current study will assess how successful a comprehensive, multifaceted educational motivation with reminder support as an intervention by using mHealth technology in improving adherence to antihypertensive therapy among hypertensive patients. It will also answer the question of improvement in adherence to medication and control of systolic blood pressure. While some studies have reported improvements in adherence to antihypertensive medications,^14^,^21^ others did not find any improvements in adherence to medication.^22^ Mixed outcomes of the intervention on medication adherence to antihypertensive treatment were revealed by a recent systematic analysis of 23 RCTs (published in 2023). A notable improvement in medication adherence was found in 73.9% of the research, while 26% of the studies did not demonstrate a meaningful influence of the intervention on medication adherence.^11^ In addition, the researcher will analyze the acceptability and efficacy of diverse clinical care aspects using this intervention. A study employed an innovative mHealth designs for CVD patients.^23^ Similarly, new mHealth models have been introduced to improve medication adherence.^24^ Traditionally, written medication schedules, peer counseling,^23^ health education,^25^ counseling,^23^ and routine check-ups have all been utilized to help hypertension patients adhere to their drug regimens.

Compared to other interventions, the current intervention is a comprehensive and novel approach that can be considered an updated version of previous material on the topic because it combines multiple aspects into a single application. According to what we know, this will be the only study to design and test the efficacy of a full, holistic mHealth approach. Furthermore, most intervention studies concentrate on patient adherence to medication rather than blood pressure control.^22^ The current study will gather data on both adherence to medication and as well as SBP, If the intervention can lower the patient’s SBP, it will be a significant improvement in clinical settings with limited resources. There are suggestions for more advanced and effective interventions to improve CVD adherence.^11^

### Limitations:

In the current study, medication adherence will be evaluated through self-reporting. Social desirability bias may lead to an overestimation of actual adherence in self-report questionnaires.

## CONCLUSION

According to this study, if the multifunctional Multi-Aid-Package proves to be a useful mobile health tool for improving hypertension patients’ medication adherence, it will also significantly affect systolic blood pressure. In addition, it will assist the patients in understanding the significance of adhering to their medication routine. The current intervention will be feasible and can easily be employed. In Pakistan and other comparable LMICs, the Multi-Aid-Package ought to be taken into consideration as a means of enhancing adherence to medications among hypertension patients.
